### Alliance and outcome

The relationship between early change, the alliance, and outcome will be examined at posttreatment and follow-up. These relationships will be analyzed in a similar manner as described in Anker et al. [33], using multilevel analysis in which the levels of patient and therapist will be taken into account. Pretreatment scores and early change will be included as covariates. Patterns in alliance scores of clients ad therapists will be examined to determine whether different patterns of alliance development differentiate outcomes, comparing clusters using chi-square analysis (clinical significant change used as cut off score) as well as ancova analysis (outcome added as a continuous measure).

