### Results of studies on alliance on feedback

Scarce studies have been performed on the specific effect of feedback on alliance in relation to outcome (Whipple [16], Harmon [38] and Slade et al. [45], Crits Christoph [37]). Fluckiger et al. (2013) [46] found that multiple interconnected components simultaneously influence the early phase of treatment, while interpersonal distress at intake as well as the early interpersonal session experiences by patients and therapists seem to be robust predictors of outcome. These findings underscore that therapists need to monitor and discuss intra- as well as interpersonal experiences early in therapy, though its interaction is not yet fully understood.

It is yet unclear whether feedback on the alliance improves alliance, and it is equally unclear whether feedback on the alliance actually boosts outcome; let alone if these mechanisms work similar in a psychiatric and psychotherapeutic settings. Subsequently, it is unknown if applying an alliance measure to a feedback system (like in PCOMS) actually contributes to the improvement of outcome.

These considerations taken into account, it is important that a future study on feedback informed treatment adds a separate instrument for measuring the quality of the alliance in both feedback and non-feedback condition. Hence making it possible in a more independent way to examine if feedback (on alliance) actually influences the quality of the alliance; and to examine the relation between separately measured alliance scores, alliance scores provided by the feedback instrument and outcome scores.

The design of this study meets this requirement by adding the Helping Alliance Questionnaire II for both client and therapist.

In summary, we can conclude the following from the studies above.

Immediate feedback would appear to be a promising method but, at the outset of our study, studies were restricted to a few specific populations such as students and partner counselling, with the level of distress at the outset of the treatment appearing to be relatively limited (with an average ORS score of about 20). The method has not yet been studied in patients with severe and acute psychiatric symptoms.

Also, it is yet unclear if feedback on alliance improves the alliance and if this process influences outcome. In feedback studies, both outcome and alliance have not yet been examined with independent measures so far.

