Taking into account all considerations mentioned before, the research questions for this study are:

1) to examine whether applying immediate feedback at each treatment session in a psychiatric population with severe distress results in better outcomes (10% fewer complaints, enhanced well-being), higher client satisfaction and a more efficient treatment (shorter treatment duration) compared with the no-feedback condition (the same therapists operating in both conditions). Outcome has to be measured with a measure independent from the instrument used in the feedback process.

2) to examine whether applying immediate feedback at each treatment session results in improvements to the alliance; and whether there is a link between any improvement in alliance and improvement in treatment outcome. Alliance to be measured with a measure independent from the instrument to be used for feedback.

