## Discussion

### Replication in other target group

Previous research has generated promising findings relating to the use of feedback in treatment. The primary distinguishing feature of this study is the target group: PCOMS has been studied previously in a student population only [29] and in couples presenting for relation therapy [30,31]. In this study, we look at a group of patients with severe psychiatric and social problems. In addition, these patients are generally going through a crisis, which is a very different situation from patients looking for psychotherapeutic assistance. An initial aim of this study is therefore to establish whether the results achieved in the past are replicated in patients with psychiatric problems in a crisis service setting. Secondly, previous studies have not used supplementary measurement instruments to assess the quality of the alliance or the level of well-being systematically. Reese et al. [29,30] use PCOMS only; Anker et al. [31] use only the Locke Wallace Marital Adjustment Test as a supplementary instrument during intake and follow-up. In this study, in addition to PCOMS, we use the BSI, OQ45, HAQ II and CGI. A second aim of this study is therefore to establish a more reliable picture of actual changes in well-being, symptom reduction and functioning, and to study the relationship between developments in the alliance, feedback and outcome measures.

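### The alliance–outcome model names its covariates without treatment arm, so a small part of any feedback effect can enter the alliance coefficient

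*Protocol article*

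**What the plan says.** Research question 2, at the end of the Background, has two halves. The first is "to examine whether applying immediate feedback at each treatment session results in improvements to the alliance". The second asks "whether there is a link between any improvement in alliance and improvement in treatment outcome". Research question 1 asks whether feedback gives better outcomes. The Discussion (Replication in other target group) joins the three elements in one aim: "to study the relationship between developments in the alliance, feedback and outcome measures".

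The analysis for the second half of question 2 is under Secondary analyses, Alliance and outcome. It is a multilevel model, "using multilevel analysis in which the levels of patient and therapist will be taken into account". Its covariates are given in one sentence: "Pretreatment scores and early change will be included as covariates". Alliance patterns are then grouped and related to outcome by "comparing clusters using chi-square analysis (clinical significant change used as cut off score) as well as ancova analysis". Neither part mentions treatment arm. The general approach is taken from an earlier published study: "These relationships will be analyzed in a similar manner as described in" that source, which is not at hand.

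The section just before it (Feedback and client and therapist variation) does name feedback. Model 2 estimates its effect and Model 3 adds a random slope for it across therapists. Neither model contains alliance. No analysis described in the article therefore holds arm, alliance and outcome together.

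**The concern.** Alliance is measured after randomisation, and the trial is built on the idea that the randomised intervention may change it. If feedback raises alliance and also improves outcome by another route, the EXP group sits higher on both variables than the TAU group. In an analysis over all patients without an arm term, that difference between groups looks like an association between alliance and outcome, even if the two are unrelated within each arm. The alliance coefficient then mixes a patient-level link with the treatment effect.

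At stake is the answer to half of a numbered research question. Arm is known for every patient, so nothing in the data forces the omission.

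The covariates that are named do not reliably remove the problem. Pretreatment scores precede randomisation and should be balanced between arms. Early change follows randomisation and may carry part of the feedback effect, but there is no reason to expect it to carry all of it.

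**Working it through.** **Inputs from the article**
- Sample size calculation: 90 patients per arm; Global Severity Index at 12 weeks 1.0 (EXP) versus 1.3 (TAU); SD 0.80; one-sided alpha 0.05; power 80%.
- The role of the alliance: early in-session relationship measures explain at least 8% to 14% of outcome variance.

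**Input assumed:** the effect of feedback on alliance, dA. The article gives no figure, so a range of 0.1 to 0.8 SD is used.

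**1. The plan's own figure.** n per arm = 2 × (1.645 + 0.842)² × 0.80² / 0.30² ≈ 88. With 90 per arm, power = Φ(0.30 / (0.80 × √(2/90)) − 1.645) = Φ(0.871) = 0.808. The stated 80% reproduces. The standardised outcome effect behind it is dY = 0.30/0.80 = 0.375, which is used below with the sign turned so that higher means better.

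**2. Correlation created by omitting arm.** With equal arms and no alliance–outcome link within either arm, the correlation over all patients is

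r = (dA × dY / 4) / √[(1 + dA²/4)(1 + dY²/4)].

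For dA = 0.3: 0.0281 / √(1.0225 × 1.0352) = 0.0281 / 1.0288 = 0.027.

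**3. Effect on the test.** By Fisher's z with N = 180, the test statistic is shifted by atanh(r) × √177. For dA = 0.3 the shift is 0.364, and a two-sided 5% test rejects with probability [1 − Φ(1.96 − 0.364)] + Φ(−1.96 − 0.364) = 0.065.

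| Assumed dA (SD) | Spurious r | Rejection at nominal 5% |
|---|---|---|
| 0.1 | 0.009 | 5.2% |
| 0.3 | 0.027 | 6.5% |
| 0.5 | 0.045 | 9.1% |
| 0.8 | 0.068 | 14.9% |

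**4. Check by simulation.** 5,000 trials of 180 patients were simulated at each of three values of dA, regressing outcome on alliance and pretreatment score. The coefficient of 0.5 for pretreatment score on outcome is assumed. Therapist level and early change were not modelled.

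| dA (SD) | Slope without arm | Rejection without arm | Rejection with arm |
|---|---|---|---|
| 0.3 | 0.025 | 6.3% | 4.3% |
| 0.5 | 0.044 | 10.4% | 5.1% |
| 0.8 | 0.065 | 18.3% | 5.1% |

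With arm in the model the mean alliance slope is about zero in all three cases (at most 0.002 in absolute value).

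**5. Scale.** The cited 8% to 14% of variance corresponds to r = √0.08 = 0.28 to √0.14 = 0.37. The spurious part is an order of magnitude smaller at dA = 0.3, and about a fifth to a quarter of it at 0.8 (0.068/0.37 = 0.18; 0.068/0.28 = 0.24).

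**6. What an interaction could show.** For correlations of 0.30 in one arm and 0 in the other, the standard error of the difference in Fisher's z is √(2/87) = 0.152 and atanh(0.30) = 0.310. The ratio is 2.04, which gives a two-sided power of about 53%.

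**The case against.** The strongest case against is that this is a condensed article. The sentence lists two covariates without saying that they are the only ones, it nowhere says that the arms are pooled, and it relies on a cited study and on later papers for detail. That stands as a reason for caution: an arm term may exist in material that is not shown. It does not settle the point. The article chose to state the covariates, names feedback explicitly in the neighbouring models, and leaves it out here.

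It is also fair that the calculation takes an extreme case. It assumes no link within arms, so the whole 0.375 SD bypasses alliance. If feedback worked entirely through alliance, there would be no confounding by arm. Early change, which is in the model, may absorb some of the rest. The upper assumed value of 0.8 SD is more than twice the planned outcome effect.

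A reader might infer more than the documents support:
- **That the link cannot be compared between arms.** It can. Under Procedures and time points, patients in both conditions complete the HAQ-II on the same schedule. The comparison is possible but is not described.
- **That an arm-by-alliance interaction is required.** The Background says that "it is equally unclear whether feedback on the alliance actually boosts outcome", and question 2 asks about a link. Neither clearly asks whether the slope differs by arm, and step 6 shows how little power there would be to tell.
- **That the bias may run the other way and hide a true link, because feedback invites criticism of the alliance.** That criticism is voiced on the SRS, a tool of the EXP arm. The independent alliance measure is the HAQ-II. The Conclusion wonders whether feedback might burden the relationship, but nowhere says that it lowers HAQ-II ratings.

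**Conclusion.** The point holds in a limited form. As written, the model has no arm term, and an effect of feedback on both alliance and outcome would enter the alliance coefficient to the extent that it does not act through alliance. At the planned outcome effect and an assumed alliance effect of 0.3 to 0.8 SD, the spurious correlation is about 0.03 to 0.07. The two-sided 5% test rejects in about 6.5% to 15% of trials (6% to 18% in the simulation that adjusts for pretreatment score). This would add a little to a real link of the size the article cites. It would not explain such a link away.

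The figures rest on the assumed alliance effect, no link within arms, and complete data on 180 patients. They also carry the 12-week effect on the Global Severity Index over to the post-treatment and follow-up outcomes that this analysis uses. Fewer patients or partial mediation through alliance would make the inflation smaller. Certainty is moderate because the cited method is not at hand. The primary comparison of EXP with TAU is unaffected.

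**What to change.** In Alliance and outcome, extend the covariate sentence so that pretreatment scores, early change and treatment arm are all included in the multilevel model. Include arm in the ANCOVA of the alliance-pattern clusters as well, and stratify the chi-square comparison by arm (for example with a Cochran–Mantel–Haenszel test). If the cited method already contains an arm term, saying so is enough.

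The alliance slope within each arm and the arm-by-alliance interaction may be reported as exploratory, with confidence intervals and a note on their low power. The interaction belongs in a separate model, because once it is included the alliance main effect refers to one arm only and no longer answers the general question.

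The cost is a line of text and one degree of freedom for arm in each regression model; no new data are needed. Stratifying may leave sparse cells if there are many clusters.

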#### Primary analysis: EXP versus TAU

In the primary analysis, outcomes of the two treatment conditions will be compared using repeated measures analysis (GLM), with the number of sessions as a covariate. In this analysis, each follow-up measurement will be compared separately to the baseline measurement. Since in this design patients are nested within therapists, these nested data will also be examined in a multilevel analysis, controlling for therapist variation. The number of sessions will be included as a covariate.

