#### Secondary analyses

The following secondary analyses will be presented in separate papers following the paper on the primary outcomes.

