### Feedback and client and therapist variation

If some therapists are generally more effective than others, then the outcomes of clients seen by the same therapists will be correlated. Three multilevel models will be constructed to examine therapist and client effects as well as the effects of feedback on posttreatment functioning, similar to the analysis by Anker et al. [31]. In Model 1, the presence of therapist and client effects will be tested by controlling for pretreatment functioning at Level 1 and evaluating the residual intraclass correlations. To determine the variance due to therapist and client, the residual intraclass (controlling for pretreatment ratings) correlation will be calculated. In Model 2, the effect of feedback will be estimated, and in Model 3 a random slope for feedback will be added to examine if the effect of feedback varies across therapists.

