### Design benefits and drawbacks

The design meets the requirements formulated by Lambert [15] and Anker et al. [31] in their study for future research into direct feedback in order to ensure that the design is as strong as possible: random allocation of patients to the different study conditions, therapists working in both study conditions, the use of different treatment methods and working with experienced (accredited) care providers.

In accordance with these principles, then, all therapists participate in both conditions to which the patients are randomised (the experimental and control conditions). They therefore treat approximately 50% of their clients using PCOMS and 50% on the basis of TAU. The benefit of this design, all therapists working in both groups, is that any differences in effectiveness between therapists cannot be a factor in differences between outcomes. Given the fact that, with regard to effectiveness, differences between therapists are larger than differences between therapeutic methods, it is important to eliminate the impact of the therapist variable in order to be able to arrive at conclusions about effects of any method [63].

Another benefit is that it is not very likely that allegiance factors (i.e. therapists being enthusiastic about the method) will affect outcomes in favour of the EXP condition because all the participants have received the same training for using PCOMS and both more, and less, highly motivated therapists deliver treatment to the EXP group. The possible drawback of this design is that, as a consequence of contaminations, any positive effects of PCOMS might not emerge as clearly. Given the fact that all therapists are working in both conditions, there is a risk that the difference between the two conditions will not be as large because the therapists in the TAU condition can ask for more feedback spontaneously, or use PCOMS less naturally in EXP condition or even forget to discuss the feedback. Another potential flaw however is that, the other way around, the design favours the EXP condition because therapists may attention more to patients in the feedback condition simply because these patients are more salient to them.

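### The secondary comparison of alliance patterns names chi-square and ANCOVA with no therapist term, so therapist differences can appear as a link between alliance and outcome

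*Protocol article*

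**What the plan says.** All relevant text is in the protocol article.

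- **Alliance and outcome.** The relationship between early change, alliance and outcome is to be analysed "using multilevel analysis in which the levels of patient and therapist will be taken into account", and "Pretreatment scores and early change will be included as covariates". For the next step, whether different patterns of alliance development separate outcomes, the tools change: "comparing clusters using chi-square analysis (clinical significant change used as cut off score) as well as ancova analysis", the latter on the continuous outcome. No therapist level is mentioned for this step.
- **Primary analysis: EXP versus TAU.** "Since in this design patients are nested within therapists, these nested data will also be examined in a multilevel analysis, controlling for therapist variation".
- **Feedback and client and therapist variation.** This section opens with its premise: "If some therapists are generally more effective than others, then the outcomes of clients seen by the same therapists will be correlated". This is a conditional statement, and the models that follow are meant to test it.
- **Design benefits and drawbacks.** The authors take as fact that "with regard to effectiveness, differences between therapists are larger than differences between therapeutic methods".
- **Secondary analyses.** "The following secondary analyses will be presented in separate papers following the paper on the primary outcomes".

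**The concern.** A chi-square test on a pattern-by-outcome table treats every patient as independent and has no place for a therapist. An ANCOVA could hold a therapist factor, but none is named.

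The design's safeguard against therapist effects is that each therapist treats patients in both arms. That balances therapists across a randomised comparison. Alliance pattern is observed, not assigned, so it can be unevenly spread over therapists. A therapist who builds strong alliances and also gets good results places patients in the good-pattern, good-outcome cell even if alliance and outcome are unrelated among that therapist's own patients.

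Chi-square also drops the two covariates that the same paragraph includes in the relationship analysis: pretreatment score and early change.

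At stake is part of research question 2, the link between alliance and treatment outcome. The pattern comparison could report a link that really reflects who the therapist was.

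**Working it through.** **Plan's own figures.** The article gives no figure for this comparison. Its power statement reproduces (90 per arm, difference 0.3, SD 0.80, one-sided 5%: 80.8% against the stated 80%), but it concerns the arms, not alliance patterns. Only the total of 180 patients is carried forward.

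**Inputs from the document.** N = 180 (Sample size calculation). Permanent therapists 6 + 10 + 2 + 1 = 19, plus an unstated number of rotating doctors (Patients in crisis). Patients per therapist with 19 therapists: 180/19 = 9.5.

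**Assumed inputs, because the document gives none.** Therapist ICC of outcome 0.05-0.2; therapist ICC of alliance 0-0.3; correlation ρ between a therapist's effects on alliance and on outcome 0 to 1; 19 to 35 therapists; one therapist per patient; no alliance-outcome link within therapist.

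**Step 1: lost independence alone.** If the two therapist effects are unrelated, the variance is inflated by roughly 1 + (m − 1) × ICC(alliance) × ICC(outcome), with m = 9.47.
- ICCs 0.2 and 0.1: 1 + 8.47 × 0.02 = 1.17.
- ICCs 0.2 and 0.2: 1 + 8.47 × 0.04 = 1.34.

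The product of two modest ICCs is small, so this route does limited harm.

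**Step 2: confounding.** If the effects are related, they induce a patient-level correlation between underlying alliance and residual outcome of ρ × √(ICC(alliance) × ICC(outcome)).
- ρ = 0.5, ICCs 0.05 and 0.05: 0.5 × 0.05 = 0.025.
- ρ = 0.5, ICCs 0.2 and 0.1: 0.5 × 0.141 = 0.07.
- ρ = 0.5, ICCs 0.2 and 0.2: 0.5 × 0.2 = 0.10.
- ρ = 1, ICCs 0.2 and 0.2: 0.20.

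This is bias, so a larger sample would not remove it.

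**Step 3: simulated type I error, two pattern groups.** 19 therapists, 3,000 runs per cell, nominal two-sided 5%. The Monte Carlo standard error at 5% is √(0.05 × 0.95/3000) = 0.4 percentage points. ANCOVA adjusts for baseline. Entries are chi-square / ANCOVA, in per cent.

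| ICC alliance, outcome | ρ = 0 | ρ = 0.5 | ρ = 1 |
|---|---|---|---|
| 0, 0.1 | 5.1 / 5.0 | – | – |
| 0.05, 0.05 | 5.3 / 5.1 | 6.3 / 6.6 | 6.5 / 7.7 |
| 0.1, 0.1 | 5.0 / 4.7 | 7.0 / 8.8 | 11.9 / 18.4 |
| 0.2, 0.1 | 5.4 / 5.6 | 9.0 / 11.7 | 17.1 / 31.5 |
| 0.2, 0.2 | 5.7 / 6.9 | 12.1 / 20.3 | 31.1 / 52.2 |

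With 30 therapists the results are similar. At ρ = 0.5, chi-square gives 5.0-12.0% and ANCOVA 5.9-19.0%. Adding therapist as a fixed factor to the ANCOVA brings every cell, with 19 or 30 therapists, to 4.2-6.1%.

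**Step 4: a second simulation, three pattern groups.** 19 to 35 therapists, 4,000 runs per scenario, outcome ICC 0.05-0.10, alliance ICC 0.1-0.3, about 40% successes, and an unadjusted F test in place of ANCOVA.
- ρ = 0: about 5-8%.
- ρ = 0.5: chi-square 6-12%, F test 6-16%.
- ρ = 0.8: chi-square 7-20%, F test 7-30%.

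The two simulations agree.

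**The case against.** - **The document does not establish the conditions for material error.** It nowhere says that alliance patterns cluster by therapist or that therapist effects on alliance and outcome are related. Every ICC and correlation above is assumed. This stands. A reader might infer that the p-values are simply wrong. The figures do not support that: with unrelated therapist effects, the error stays near nominal.
- **The plan does not assert that outcomes are correlated within therapist.** The sentence in Feedback and client and therapist variation is an if-then. This stands too, although the nesting and the therapist differences in effectiveness are asserted elsewhere.
- **The simulations are not exactly the planned analysis.** Early change was not modelled and might absorb part of a therapist effect. Each simulated patient had one therapist, whereas the TAU section says two where possible, and Patients in crisis adds co-therapy, shifts and staff changes. The figures therefore indicate scale; they do not predict the error rate.
- **Separating outcomes can be read as a predictive question.** On that reading, an overall association that includes differences between therapists is a legitimate answer. This is a reason to report both associations. It does not justify leaving the therapist out.
- **The article is condensed.** The full plan may put a therapist factor in the ANCOVA. That cannot be excluded for the ANCOVA, but the chi-square test is named outright and cannot carry one.

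**Conclusion.** The point holds for the alliance-pattern comparison only. The named tests do not match the multilevel approach of the same paragraph, and the design gives no protection because alliance pattern is not randomised. The main risk is confounding by therapist; understated standard errors matter less.

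Its size depends on quantities that the document does not give. With outcome ICC 0.05-0.2 and alliance ICC up to 0.3, type I error is about 5-8% if therapist effects on alliance and outcome are unrelated, and about 6-20% at a correlation of 0.5. The weakest such cell, 30 therapists and both ICCs 0.05, shows no inflation for chi-square. The error is higher at stronger correlations: up to about 30% at 0.8, and up to about half at the extreme of 1.

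A reader might conclude that research question 2 as a whole is compromised. It is not: the main alliance-outcome relationship is already planned as multilevel, and this comparison is secondary and reserved for later papers. The primary analysis is untouched.

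**What to change.** Replace chi-square and ANCOVA by the multilevel framework already named in the paragraph:

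1. Use a mixed logistic model for clinically significant change and a mixed linear model for the continuous outcome, with alliance pattern as predictor, a therapist random effect, pretreatment score and early change.
2. State how co-therapy is handled: assign each patient to a primary therapist by a rule set in advance, or use a multiple-membership term.
3. Report the overall association and, beside it, the within-therapist association, obtained by adding the therapist's mean alliance (for categorical patterns, the share of that therapist's patients in each). A random intercept alone removes the between-therapist part only partly.

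**Cost.** New wording, modest extra analysis work and somewhat wider intervals; no new patient data. With about 5 to 9 patients per therapist (180/35 to 180/19), therapist means will be noisy, so the between-therapist coefficient should be read with caution.
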